### Sensitivity analyses

#### Sensitivity to the no unmeasured confounders assumption

Our analysis relies on the assumption that there are no unmeasured confounders. Unfortunately, there may exist some factors that are associated with both treatment prescription and outcome, which are not captured in the registries (denoted by U in figure 2). Sensitivity to unmeasured confounders will be summarised using E-values.^29^

#### Allowing individuals to enter the emulated trials more than once

For the main analysis, individuals will be included in the emulated trial once. Individuals ‘enter’ the trial at time 0, which is defined as the earliest year within the recruitment period that they meet the inclusion and exclusion criteria. This approach restricts the analysis to using information from everyone at one time point only and may be inefficient. Alternatively, we can allow individuals to ‘enter’ the trial twice if they meet the inclusion and exclusion criteria in both years during the recruitment period. Standard errors will need to take into account that individuals are included multiple times.

### Missing data

The amount of missing data in each variable will be summarised in tables by treatment group. Where there are missing data in binary time-varying variables that are usually static for long time periods, we will use a simple imputation approach. For missing visits where the prior visit and subsequent visit are equal, we will assume the missing value is also equal and impute accordingly. This approach will be used for the following variables: pancreatic insufficiency, *P. aeruginosa*, *S. aureus*, NTM, CFRD, inhaled antibiotics, inhaled steroids, hypertonic saline and DNase. Missingness patterns in the remaining missing data will be explored. If there are missing outcomes that are missing at random conditional on C, then a complete case analysis is appropriate.^28^ If a complete case analysis is not appropriate, more complex missing data methods such as multiple imputation by chained equations^30^ may be considered.

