#### Causal estimand of interest

The target trial reported the difference in mean changes (between month 0 and month 12) in FEV_1_% between treatment groups in the total population:

(1)
$$ATE=E\{Y_{1}(1)-Y_{0}(1)\}-E\{Y_{1}(0)-Y_{0}(0)\}$$

where the expectations refer to the population of individuals meeting the criteria for the target trial. This is equivalent to the difference in means at the end of follow-up as the observed value of Y at time 0 is unaffected by treatment, that is, $Y_{0}\left(a\right)=Y_{0},i.e.$

(2)
$$ATE=E\{Y_{1}(1)\}-E\{Y_{1}(0)\}$$

Our causal estimand is interpreted as the expected difference in FEV_1_% at month 12 if everyone had taken azithromycin for 12 months, compared with a scenario where no one took azithromycin for 12 months.

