#### Main analysis

In the target trial, the authors investigated the change in FEV_1_% from baseline, with adjustment for baseline FEV_1_%. This is equivalent to a regression of the mean FEV_1_% at follow-up with adjustment for baseline FEV_1_%. We note that in the absence of imbalance between treatment groups in baseline FEV_1_%, the adjustment of baseline FEV_1_% is not required but may result in gains in efficiency. Both approaches result in estimates of the ATE as defined in equations(1)  (2).

In the emulated trials, we need to account for differences between treatment groups at baseline, including baseline FEV_1_%. We also require assumptions of positivity, no interference, consistency and conditional exchangeability (conditional on C). We use augmented inverse-probability-of-treatment weighting (AIPTW) to control for potential confounding by C. AIPTW involves defining models for the treatment and outcome. This approach was chosen as it is doubly robust, meaning that it gives consistent estimates of treatment effects if either the treatment model or outcome model is correctly specified.^27^ This represents an advantage compared with the alternative propensity score or outcome-regression based approaches which are singly robust.

The first step in implementing AIPTW is to estimate the propensity scores, that is, the probability of treatment conditional on baseline covariates:

(3)
PS=P(A=1|C)

Propensity scores will be estimated using logistic regression, including C as linear terms.

In the second step, we specify an outcome model conditional on treatment and covariates:

(4)
$$Y_{1}=\gamma_{0}+\gamma_{A}A+\gamma_{C}C+\varepsilon$$

The AIPTW estimator for

(5)
$$\hat{E}[Y_{1}(a)]=\frac{1}{n}\sum_{i=1}^{n}\left\{\frac{I(A_{i}=a)Y_{1i}}{\hat{P}(A_{i}=a|C_{i})}-\frac{I(A_{i}=a_{i})-\hat{P}(A_{i}=a|C_{i})}{\hat{P}(A_{i}=a|C_{i})}\hat{E}(Y_{1i}|A_{i}=a,C_{i})\right\}$$

where $\hat{P}(A_{i}=a_{i}|C_{i})$ can be obtained using predictions from the propensity score model. The estimator in equation 5 can be used to estimate $E\left[Y_{1}\left(0\right)\right]$ and $E[Y_{1}(1)],$ and the difference between these two expectations is an estimate of the average treatment effect in the population. Standard errors can be obtained based on the efficient influence function.^28^

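### Missing at random given C does not by itself make complete-case AIPTW estimate the ATE the plan defines; effect modifiers that predict missing FEV1% would shift it

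*Protocol article*

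**What the plan says.** The Missing data section of the protocol article first summarises missingness by treatment group, fills in some static binary covariates, and explores the remaining patterns. It then gives a rule for outcomes: "If there are missing outcomes that are missing at random conditional on C, then a complete case analysis is appropriate". Other methods come in only if that rule fails: "If a complete case analysis is not appropriate, more complex missing data methods such as multiple imputation by chained equations" may then be considered.

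The section Causal estimand of interest defines the ATE as a marginal difference in means, "where the expectations refer to the population of individuals meeting the criteria for the target trial", and interprets it as "the expected difference in FEV_1_% at month 12 if everyone had taken azithromycin for 12 months" compared with no one taking it.

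The Main analysis section estimates this by AIPTW. The propensity model is logistic and linear in C. Equation 4 contains main effects of A and C and no interaction between them. Equation 5 averages over n people with weights for treatment only, and the article says that "the difference between these two expectations is an estimate of the average treatment effect in the population". AIPTW is preferred because "it gives consistent estimates of treatment effects if either the treatment model or outcome model is correctly specified".

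Table 2 and the section on time 0 and the index visit make a follow-up visit an eligibility criterion.

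**The concern.** Missing at random given C protects a regression in which C is held fixed. The reported quantity is different: it averages effects over people. If the chance of an observed outcome depends on C, which the rule allows, the complete cases have a different mix of C from all eligible people. Nothing in equation 5 brings the average back to the full group.

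The rule also steers away from a remedy. Imputing outcomes for all eligible people would restore the right average, but imputation is reserved for the case where complete cases are judged inappropriate, and the rule has just judged them appropriate under missingness at random given C.

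At stake is the comparison with the target trial and between registries and periods. Missingness may differ between these datasets, so each complete-case estimate could refer to a somewhat different population. Part of a gap could then be read as residual confounding or failed emulation.

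**Working it through.** The article states no figure on this point, so there is none to reproduce.

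**Inputs from the article:** the ATE over all eligible people (equation 2), the outcome model (equation 4), the estimator (equation 5), and the missing-data rule. **Assumed, because the article gives neither:** the share of outcomes missing and how the effect varies with C.

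**Limit of equation 5 on complete cases.** Let R = 1 if FEV1% at time 1 is observed, τ(C) = E[Y1(1) − Y1(0) | C] and π(C) = P(R = 1 | C). Under missingness at random and the plan's own exchangeability assumption, the complete-case estimator converges to E[τ(C) | R = 1]. The ATE is E[τ(C)]. Their difference is

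Cov{τ(C), π(C)} / P(R = 1),

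which is zero if τ is constant, if π is constant, or if the two are uncorrelated.

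**Four assumed scenarios with a binary modifier.** The complete-case limit weights each subgroup's effect by (subgroup share × proportion observed).

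| Effect: subgroup / rest | Subgroup share | Missing: subgroup / rest | Missing overall | ATE | Complete-case limit | Shift |
|---|---|---|---|---|---|---|
| 5 / 1 | 40% | 10% / 40% | 28% | 2.6 | (0.36×5 + 0.36×1)/0.72 = 3.00 | +0.40 (+15%) |
| 5 / 1 | 40% | 40% / 10% | 22% | 2.6 | (0.24×5 + 0.54×1)/0.78 = 2.23 | −0.37 (−14%) |
| 4 / 2 | 40% | 10% / 30% | 22% | 2.8 | (0.36×4 + 0.42×2)/0.78 = 2.92 | +0.12 (+4%) |
| 5 / 0 | 30% | 5% / 35% | 26% | 1.5 | (0.285×5 + 0.455×0)/0.74 = 1.93 | +0.43 (+28%) |

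Simulating these settings (20,000 people, 60 replicates each, logistic propensity model, main-effects outcome model) gave complete-case estimates of 3.00, 2.22, 2.93 and 1.91. With the added weight for being observed and the average taken over all n, the estimates were 2.59, 2.59, 2.81 and 1.47, close to the true values.

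**A continuous modifier.** A second simulation used 200,000 people per setting and a true ATE of 2.0, with noise of about 0.05:

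- Constant effect: complete-case equation 5 gave 1.95 to 2.04, even with strong selection on C.
- Observation unrelated to C, effect varying: 1.96 to 2.04.
- Log-odds of observation 0.5 per SD of C, effect changing by 1, 2 or 3 points per SD: about 2.1, 2.2 and 2.3.
- Log-odds 1 per SD of C (24% to 27% missing), same effect changes: about 2.2, 2.3 to 2.4, and 2.6.
- Two corrected analyses averaging over all eligible people (observation-weighted AIPTW, and an outcome model with interaction standardised to everyone) gave 1.89 to 2.04 across all settings. Estimates from the full data were 1.91 to 2.06.

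**The case against.** The strongest reply is that equation 4 has no treatment-by-covariate interaction. If it is correct, the effect is constant and complete cases are consistent for the ATE, as the simulation confirms. No part of the article reports or posits effect modification. This stands as a condition on the point: a reader might infer that complete cases always miss the ATE, and the documents do not support that. It does not rescue the rule, because AIPTW was chosen to remain consistent when equation 4 is wrong and the propensity model is right. On complete cases with a varying effect, that protection no longer delivers the ATE defined in the plan.

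A reader might also infer that the imputation fallback has the same defect. It does not. The article names no imputation variables, so predictors beyond A and C are allowed, and imputing for all eligible people averages over the full covariate distribution. What remains is narrower: if missingness at random given A and C is doubted, imputation helps only if it adds predictors beyond A and C.

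Nor is this a point about loss to follow-up in general. People without a follow-up visit are excluded before the rule applies, and the remedy here does not bring them back.

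Finally, the scenarios are assumed and some are strong. Against the target trial's imprecision the shifts are small. Its confidence interval is not in the article; assuming an SD of 8 to 15 points for 12-month change and its 40 and 42 participants, the standard error is SD × √(1/40 + 1/42) = 1.8 to 3.3 and the 95% half-width 3.5 to 6.5. A shift of 0.12 to 0.43 is about 2% to 12% of that half-width and moves the standardised difference by at most 0.43/1.77 = 0.24. The agreement criteria based on the interval and the standardised difference would change only in borderline cases. That objection stands. The rule is also provisional, since missingness patterns are explored first, and the source cited for it was not available to check.

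**Conclusion.** The stated condition is insufficient for the estimand. Missingness at random given C makes complete-case equation 5 consistent for the effect in people with an observed outcome. That equals the ATE only if, in addition, the effect is unrelated to the covariates that drive missingness. The rule omits this second condition, and the plan's reliance on double robustness means it should not be borrowed silently from equation 4.

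The size is unknown and may be small. It is zero under a constant effect, about 0.1 to 0.4 FEV1% points in the assumed subgroup scenarios, and about 0.6 in the most extreme continuous one (3 points per SD of C, log-odds of observation 1 per SD). All of these assume roughly a quarter of outcomes missing, which the article neither states nor implies. The scope is mainly FEV1% missing among people who attended a follow-up visit. A reader might infer that the comparison with the target trial is invalid; the documents do not support that. The case for changing the rule is that the better estimator is cheap.

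**What to change.** Replace the complete-case sentence with a rule along these lines. Under missingness at random given A and C, keep every eligible person with A and C recorded in equation 5, whether or not FEV1% at time 1 is observed. Fit the propensity model in all of them and equation 4 in those with an observed outcome, giving predictions m_a(C). Estimate P(R = 1 | A, C) by logistic regression. Then estimate E[Y1(a)] by the mean over all n of

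m_a(C) + I(A = a, R = 1) / [P(A = a | C) × P(R = 1 | A = a, C)] × {Y1 − m_a(C)},

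with standard errors from the influence function of this extended estimator. Multiple imputation of outcomes for all eligible people, followed by equation 5, is an acceptable alternative.

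Add that, if missingness at random given A and C is doubted, imputation will include predictors beyond A and C, for example FEV1% from interim US stable visits or dated intravenous antibiotic courses.

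The cost is a change of wording and one extra logistic model on data already held. The downside is one more working model: if equation 4 is wrong, both the propensity and the observation model must be right. The weights will also be slightly more variable, and the weight diagnostics already planned can cover them.

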### Comparison of results against the target trial

We will compare our results with those from the target trial with the aim of determining whether results from the emulated trials are compatible with the target trial. The following criteria will be considered, as were used in the RCT DUPLICATE Project:^8^

Do the estimated ATEs from the emulated trials replicate the direction and statistical significance of the estimated ATE in the target trial?Do the estimated ATEs from the emulated trials lie within the 95% CIs for the ATE estimates reported in the target trial?Is there evidence against the null hypothesis of no difference between the ATE estimates from the emulated trials and those from the target trial? To assess this, we calculate the standardised mean difference between the effect estimate obtained in the target trial and that obtained in the emulated trial. Evidence against the null hypothesis at the 5% level is indicated by a standardised mean difference greater than 1.96.

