**Methods and analysis:**

The target trial is a published randomised controlled trial which found evidence for beneficial effects of azithromycin use on lung function in young adults with CF. Two emulated trials are planned: one using data from the UK CF Registry and one using data from the US CF Registry. The inclusion and exclusion criteria, treatment and outcome definitions, follow-up period, and estimand of interest are all designed to match the published trial as closely as possible. The analysis step of the trial emulations will use causal inference methods to control for confounding. Results obtained in the emulated trials using registry data will be compared with those from the target trial.

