### Sample size

The target trial included 82 individuals (40 in the treated group and 42 in the placebo group). The authors note in their discussion that it is possible the study was not adequately powered to detect significant differences in FEV_1_%.

We have not performed sample size calculations for the emulated trials, and there is some debate as to whether sample size calculations are needed in studies using observational data.^33^,^35^ We plan to use all the available data in the UK CF Registry or US CF Registry and expect much larger sample sizes than were used in the target trial.

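### The test of emulated against target estimates omits the absolute value, and the first criterion asks for agreement in significance with an 82-patient trial

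*Protocol article*

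**What the plan says.** Under Comparison of results against the target trial, the article lists three questions for judging whether emulated and target results are compatible. It introduces them with "The following criteria will be considered, as were used in the RCT DUPLICATE Project".

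- Criterion 1: "Do the estimated ATEs from the emulated trials replicate the direction and statistical significance of the estimated ATE in the target trial"
- Criterion 2: "Do the estimated ATEs from the emulated trials lie within the 95% CIs for the ATE estimates reported in the target trial"
- Criterion 3 concerns the "null hypothesis of no difference between the ATE estimates from the emulated trials and those from the target trial". For this, "we calculate the standardised mean difference between the effect estimate obtained in the target trial and that obtained in the emulated trial", and then: "Evidence against the null hypothesis at the 5% level is indicated by a standardised mean difference greater than 1.96".

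The section gives no order of subtraction, no absolute value and no denominator for the standardised difference. It has no rule for combining the three answers.

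The Sample size section (under Limitations) gives 40 treated and 42 placebo patients. It reports the target trial's authors as noting that "it is possible the study was not adequately powered to detect significant differences in FEV_1"%, and it expects far larger registry samples. The Abstract (Methods and analysis) says the target trial "found evidence for beneficial effects of azithromycin use on lung function in young adults with CF". The target trial's FEV1% estimate and CI are not stated in the article.

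**The concern.** The primary objective is to assess how far the target trial's results can be replicated, and this section is where the article says how that will be judged. Two parts of it do not do what they say.

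First, criterion 3 pairs a null without direction and a 5% level with a rule that, as worded, rejects on one side only. An analyst who codes the sentence as it stands gets a different test from the one announced. Which direction goes untested depends on a subtraction order that nobody has fixed.

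Second, significance depends on sample size. Asking a large registry study to reproduce the significance of a small trial mixes two questions: whether the effects agree, and whether the studies have similar precision. The second is already known to have the answer no. The article names sample-size differences as a reason for differing results (Limitations) but does not connect this to criterion 1.

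The significance benchmark is also unclear. The Abstract's statement of benefit on lung function and the Sample size remark on power leave a reader unsure which FEV1% result criterion 1 should match.

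**Working it through.** **Inputs from the article:** 5% level, cutoff 1.96, 40 v 42 patients, registry samples much larger.

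**Assumptions, because the article gives no figures:** 200, 500 or 1000 per arm in the emulation; true effects of 0.2 to 0.5 SD; independent, normally distributed estimates with a common SD; unadjusted standard errors.

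**1. Level of criterion 3.** Two-sided: 2 × [1 − Φ(1.96)] = 2 × 0.0250 = 0.0500, which reproduces the stated 5%. Literal wording: 1 − Φ(1.96) = 0.0250, which does not. A deliberate one-sided 5% test would use 1.645. So 1.96, 5% and a no-difference null fit together only as a two-sided test.

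**2. What the missing absolute value does.** With 500 per arm, the SE of the difference between the two estimates is √(1/40 + 1/42 + 2/500) = √0.0528 = 0.2298 SD. For a true discrepancy of 0.8 SD, 0.8/0.2298 = 3.48.
- Two-sided rule: flagged with probability Φ(3.48 − 1.96) = 0.94 in either direction.
- Literal rule: 0.94 in one direction, about 0 in the other.
- Criterion 2: the target CI half-width is 1.96 × √(1/40 + 1/42) = 1.96 × 0.2209 = 0.433 SD. An over-estimate of 0.8 SD falls outside it with probability Φ((0.8 − 0.433)/0.2298) = Φ(1.60) = 0.94.

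**3. Criterion 1 when both studies share the same true effect d.** Target trial power is 1 − Φ(1.96 − d/0.2209) + Φ(−1.96 − d/0.2209). The emulation uses SE √(2/n) with n per arm. Agreement means both significant in the same direction, or both non-significant with the same sign. With n = 500:

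| d (SD) | Target power | Agree on direction and significance | Target non-significant, emulation significantly positive |
|---|---|---|---|
| 0.2 | 0.148 | 0.206 | 0.754 |
| 0.3 | 0.274 | 0.275 | 0.724 |
| 0.4 | 0.441 | 0.441 | 0.559 |
| 0.5 | 0.619 | 0.619 | 0.381 |

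At d = 0.2, agreement is 0.389 with 200 per arm and 0.149 with 1000, so a larger registry makes it worse. At d = 0.5 it stays at 0.619 for all three sizes. Under the same truth, criterion 2 is met with probability 0.926, 0.940 and 0.945 for 200, 500 and 1000 per arm. It does not have this defect.

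**4. Limit set by the target trial.** With an unlimited registry, the SE of the difference is the target trial's own 0.2209 SD. The discrepancy detectable with 80% power is (1.96 + 0.84) × 0.2209 = 0.62 SD. Criteria 2 and 3 then coincide, and a bias of 0.4 SD passes both with probability 1 − 0.441 = 0.56. If the relevant SD were 6 to 15 FEV1% points (an assumption), 0.62 SD would be 3.7 to 9.3 points.

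**The case against.** On criterion 3, the intention is not in real doubt: a no-difference null, a 5% level and 1.96 describe a two-sided test. A reader might infer that over-estimation of benefit would never be noticed. The article does not support that. The direction is not fixed, and criterion 2 is two-sided and catches large over-estimation about as often as a corrected criterion 3 would (step 2). What stands is a wording error in a stated threshold.

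On criterion 1, a reader might infer that an emulation reproducing the target estimate exactly could be declared a failed replication. The article has no pass or fail verdict. The criteria are to be considered together, and the stated objective is the extent of replication. An emulation matching a non-significant target estimate would miss only the significance part of criterion 1 and would meet direction, criterion 2 and criterion 3. It remains true that this part gives a negative answer for a reason unrelated to validity.

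A reader might also infer that the target FEV1% result was non-significant and the Abstract is therefore wrong. The article says only that inadequate power was possible, and the Abstract speaks of lung function in general. The two statements sit uneasily together, but the article alone cannot settle them.

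Finally, the target trial's wide interval cannot be designed away, and the criteria follow an earlier replication project. The Main analysis section says the target analysis adjusted for baseline FEV1%, so in raw-SD units the 0.62 SD may be too large. These points are fair. They bear on how the result is read and do not justify demanding an equivalence margin.

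**Conclusion.** The point holds in limited form. Criterion 3 as printed is a 2.5% one-directional rule labelled as a 5% test of no difference; with the absolute value the level is 5%. The significance part of criterion 1 is a poor measure of agreement here. For identical true effects of 0.2 to 0.5 SD and 500 per arm, agreement on direction and significance has probability of about 0.21 to 0.62. Those probabilities rest on assumed effects and registry sizes, independence, and unadjusted standard errors.

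Criteria 2 and 3 are reasonable checks, but absence of a significant difference is weak evidence of agreement when the target trial limits detection to about 0.62 SD. The article does not show that the criteria as a set would miss over-estimation, that any single criterion decides replication, or that the Abstract misstates the target result.

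**What to change.** - Criterion 3: write |standardised difference| > 1.96 and define the denominator as the square root of the sum of the two squared standard errors. The Diagnostics section uses the same term, standardised mean difference, for covariate balance, so the definition also removes an ambiguity.
- Criterion 1: keep agreement in direction; report agreement in significance as descriptive only.
- Report emulated minus target ATE with its 95% CI, and say that a non-significant difference is not proof of agreement.
- State the target trial's FEV1% estimate and CI so that the benchmark is fixed, and reconcile the Abstract and Sample size statements against it.

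The cost is a few sentences and two figures from the published trial; no new data or analyses of a new kind are needed. The changes should be made before emulated results are seen. The drawback is that the FEV1% comparison may have to be reported as inconclusive.
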